### Secondary outcomes

Secondary outcomes are knee pain 3 months after the end of treatment, physical function, disease severity, quality of life, muscle performance, knee pain and effort perceived during exercises, patient adherence, and satisfaction with treatment.

Knee pain 3 months after the end of treatment will be measured by VAS, as described in the primary outcome.

Physical function will be evaluated through tests recommended by the Osteoarthritis Research Society International: 30-s chair stand test, 40-m fast-paced walk test, stair climb test, and timed up-and-go test [35].

Disease severity will be measured by Lequesne’s algofunctional questionnaire, a tool composed of 10 questions regarding pain, discomfort, and function. The sum of the scores is classified as little (1–4 points), moderate (5–7 points), severe (8–10 points), very severe (11–13 points), and extremely severe (≥14 points) dysfunction [36].

Quality of life will be evaluated through the SF-36 questionnaire, a tool composed of 36 items regarding functional capacity, physical aspects, pain, general health, vitality, social aspects, emotional aspects, and mental health. The total score varies from 0 to 100, and higher indexes are related to better quality of life [37].

Bilateral muscle performance measures will be the 7–10 RM test, isometric and isokinetic torque, and rate of torque development (RTD) of knee flexors and extensor muscles. Participants will be instructed to report any pain during the assessments during these measures and whether pain has prevented them from achieving maximum strength [20]. The 7–10 RM test will be performed as previously described to determine the estimated 1-RM.

Isometric and isokinetic torque will be evaluated by isokinetic dynamometer (Biodex Multi-Joint System 3, Biodex Medical System Inc., Shirley, NY, USA) and conducted by a trained researcher. To minimize the possible influence of fatigue on muscle performance, there will be at least a 2-day interval between the 7–10 RM test and torque assessments. A 5-min warm-up will be performed before the evaluations on a stationary bicycle followed by a pre-test (three isometric and isokinetic sub-maximal repetitions). The volunteers will be positioned in the isokinetic dynamometer chair following the recommendations of the equipment manufacturer and with the dynamometer rotation axis aligned with the rotation axis of knee joint (lateral femoral epicondyle), and the torque evaluations will be initiated on the non-affected side (or on the less affected side for subjects with bilateral OA).

Isometric torque will be evaluated first. The subjects will perform three maximal isometric actions with the knee flexed at 60° for extensor analysis and 35° for knee flexor analysis (0° = total extension). Volunteers will be previously and carefully guided with standardized verbal stimulation to contract as fast and strong as possible after the command “go”, hold the contraction for 5 seconds, and relax after the command “stop”. Six attempts (three for the flexors and three for the extensors) will be performed in each limb with a 30-s interval between attempts [38]. Two minutes after isometric evaluation, the volunteers will remain positioned for concentric isokinetic evaluation (five repetitions with 60°/s speed) of the knee flexor and extensor muscles [18, 19]. Volunteers should extend and flex the knee in a pre-established range of motion (90° to 10°). The RTD will be extracted from the isometric torque curve of evaluated muscles. RTD provides physiological information such as the role of neural and muscular factors in producing strength and neuromuscular fatigue [39, 40]. Analysis of the rate of force development will be conducted as previously proposed [38, 39].

Knee pain during exercise will be assessed at all sessions (immediately after each series) by the VAS. Volunteers will be questioned regarding anterior knee pain during the last five repetitions of each series and will be informed that this pain assessment has no relation to occlusion discomfort or perceived exertion [15]. An average will be calculated to obtain the level of pain per session.

Perceived effort will be evaluated in all of the sessions through the modified 10-point Borg scale [41] immediately before starting the hack machine squatting and leg extension exercises (for baseline recording) and after the last thigh muscle–strengthening exercise. Adherence to treatment will be assessed by calculating the percentage of sessions completed by each volunteer [20].

The participants’ satisfaction with treatment will be inferred from the global perceived effect (GPE) scale and from the sensation of pleasure/displeasure during exercises. The GPE scale evaluates the clinical change perceived by the patient, comparing the onset of symptoms with the last days. This numerical scale consists of 11 points (from −5 to +5: −5, extremely worse; 0, without modification; +5, fully recovered). Higher scores indicate better recovery of the condition [42, 43]. The pleasure/displeasure related to the squatting exercise on the hack machine and leg extension will be evaluated by the Feeling Scale, a scale of 11 points, ranging from −5 (much displeasure) to +5 (much pleasure). The Feeling Scale will be applied once per session immediately after the last thigh muscle–strengthening exercise, immediately after perceived effort evaluation. The outcome measures will be conducted by the same evaluator throughout the study, and all equipment will be calibrated before starting the study.

### Masking/blinding

Participants will be masked for the intervention they receive and will be instructed not to talk about their experience during the exercise if they incidentally encounter other participants. Furthermore, the study interventions and measurements will occur in separate locations and the treatment sessions will be individualized, thus facilitating the blinding of participants and evaluators. Participants from both groups will receive the TRP evaluation to induce the placebo effect and will be informed that BFR during exercise is effective in increasing muscle strength and reducing knee pain.

### Sample size estimates

It is estimated that a sample size of 32 patients per group would be necessary to test our research hypothesis on the primary outcome (knee pain). The parameters utilized to sample size calculation included an intergroup variability (σ) in the VAS gain of 21% for both groups [44]; a non-inferiority limit (d) of 14%, which is less than the minimum clinically perceptible difference, usually considered to be 15% for the VAS [45]; a type-I error of 5% (α =0.05); a power of 80% (β=0.20) and a dropout rate of 15%.

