**Methods:**

This two-arm, prospectively registered, randomized controlled trial with blinded assessors and volunteers will involve 40 patients with knee OA. Two weekly treatment sessions will be provided for 12 weeks. Patients will perform very low-load (10% of 1-RM) and low-volume BFR exercise or HIRE (60% of 1-RM) for strengthening thigh muscles. The primary outcome will be the knee pain measured after 12 weeks of treatment. The secondary outcomes include knee pain 6 months after randomization, physical function, disease severity, quality of life, muscle performance, knee pain and perceived exertion during exercise, adherence, and patient satisfaction with treatment.

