### Inclusion and exclusion criteria

A total of 40 men and women with unilateral or bilateral knee OA diagnosed according to the American College of Rheumatology criteria will be considered eligible if they:are at least 50 years of age;are in the postmenopausal period (for women);are between 1.50 and 1.75 m in height;have a body mass index between 18.5 and 35 kg/m^2^;have moderate to very severe knee OA (score between 5 and 13 on the Lequesne Questionnaire);have a score of at least 24 on the Mini-Mental State Examination;do not have peripheral vascular disease, systolic blood pressure greater than 160 or less than 100 mm Hg, diastolic blood pressure greater than 100 mm Hg, deep vein thrombosis, diabetes, history of myocardial infarction, stroke in the previous year, or history of cancer that has generated limitations to exercise;do not have other orthopedic/neurological diseases that affect gait and do not present any other inflammatory myoarticular disease;have not undergone surgery or any invasive procedure on the knees in the previous 6 months;have not participated in physiotherapeutic treatment or lower-limb strengthening programs in the past 3 months;are not practicing regular physical activity (two or more times per week) for lower limbs (except for those who only practice walking).

Participants will be excluded if they:experience pain that completely prevents them from performing the exercises proposed by two consecutive or three non-consecutive sessions or refuse to remain in the study;begin taking specific medications that are for OA or that interfere with study outcomes;begin to exercise or perform other treatment modalities for knee OA after initiating treatment.

Patients will be able to maintain treatment with stable doses of anti-inflammatory or other medications of regular use in the 3 months prior to the start of the study [15, 23] but should avoid using medications on evaluation days. Subjects who discontinue participation in the study will be invited to participate in the assessments 3 months after the start of treatment, and 6 months after the randomization. Thus, all individuals will be included in the intention-to-treat analysis. Therapists who deliver the intervention will be eligible if they have undergone specific training for the treatment protocol.

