## Discussion

This trial will examine whether BFR resistance exercise with very low load and low volume will present effects similar to those of the HIRE on pain, muscular performance, physical function, disease severity, and quality of life in patients with knee OA. Although previous studies have shown positive effects of BRF exercises, the true efficacy of this intervention is hampered by the matching of the total exercise volume compared with HIRE [14]. In addition, no study has evaluated the effects of BFR exercise with very low load (10% of 1-RM) and low volume in patients with knee OA. If effective, BFR exercise with 10% of 1-RM can be an interesting treatment for generating lower joint overload and consequently lesser pain during exercise.

The present study can be considered of high methodological quality because it is randomized and prospectively registered, masks the evaluators and patients, concealed allocation, and used an intention-to-treat approach. Sample size was calculated to provide adequate statistical power to identify possible differences in the study primary outcome. In addition, the 3-month follow-up will enable verification of the persistent effects of BFR exercise in patients with knee OA, thus filling this gap since studies on this topic generally assess the effects only immediately after treatment.

The exercise load will be periodically adjusted, thus maintaining the overload principle of strength training. We will estimate the 1-RM from a submaximal test (7–10 RM test) to minimize the pain interference in the load determination. In addition, to avoid a possible measurement bias (gain strength due to learning with the test and not due to neuromuscular adaptations) we choose to measure the strength in three different ways (isometric, isokinetic and 7-10 RM test). [46]. Another strength of this trial is external validity. In order to enable extrapolation of the study findings to a larger portion of the population, it was decided not to limit the participation of patients according to gender, unilateral or bilateral involvement, and the use (or not) of medications. The randomization will be balanced and the statistical analysis will be adjusted according to these factors to minimize possible confounding factors due to this greater sample coverage.

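### The sample size calculation requires 64 patients but the trial is set at 40, where non-inferiority power is about 62%, not 80%

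*Protocol article*

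**What the plan says.** The protocol article gives two enrolment figures.

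- **Sample size estimates:** "a sample size of 32 patients per group would be necessary to test our research hypothesis on the primary outcome". The inputs are "an intergroup variability (σ) in the VAS gain of 21% for both groups", "a non-inferiority limit (d) of 14"%, "a type-I error of 5% (α =0.05"), power of 80% and dropout of 15%.
- **Abstract, Methods:** "randomized controlled trial with blinded assessors and volunteers will involve 40 patients with knee OA".
- **Inclusion and exclusion criteria:** "A total of 40 men and women with unilateral or bilateral knee OA".

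The Discussion then says: "Sample size was calculated to provide adequate statistical power to identify possible differences in the study primary outcome".

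No section explains why 40 replaces 64, describes the trial as a pilot, or reports the power at 40.

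**The concern.** Two arms of 32 make 64. The abstract and the eligibility section independently say 40, so this is hard to dismiss as one slip of the pen. Both figures cannot describe the same trial.

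If 40 is what will be recruited, the design no longer has the error rates it was built on. The calculation accepts a 20% risk of failing to show non-inferiority when the two exercise programmes are truly equal, and at 40 patients that risk is well above 20%. The trial's purpose is to show that the low-load programme gives similar pain results. A reader who relies on the sample size section and the Discussion would take an inconclusive result as evidence about the treatment, when it may only reflect too little information.

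**Working it through.** **Inputs**, all from Sample size estimates: SD of the VAS gain 21, margin 14, alpha 0.05, power 0.80, dropout 15%. Three assumptions are added: 1:1 allocation, a true difference of zero, and a one-sided 5% alpha. The protocol does not state sidedness. One-sided 5% is the level that reproduces its figure.

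**1. Reproduce the plan's figure.**

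n per group = 2 × (z₀.₉₅ + z₀.₈₀)² × SD² / margin² = 2 × (1.645 + 0.842)² × 21² / 14² = 27.8, so 28 evaluable.

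Dropout: 27.82 × 1.15 = 31.99, so 32, as stated. Dividing instead, 28 / 0.85 gives 33.

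Alternatives do not give 32. One-sided 2.5% needs 36 evaluable (42 to 43 with dropout). Equivalence by two one-sided 5% tests needs 39 evaluable (about 46 with dropout).

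So 32 is a per-group figure that already includes dropout. It cannot be a total for both groups.

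**2. Size of the gap.**

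- Enrolled: 64 − 40 = 24 patients, and 24/64 = 37.5%.
- Evaluable: 2 × 28 = 56 needed. With 15% dropout, 40 × 0.85 = 34 are available.
- Even 40 with no dropout is below the 56 needed before any dropout allowance.

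**3. Power at the stated enrolment.**

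SE = 21 × √(2/n); power = Φ(14/SE − z).

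- n = 17: SE = 7.20; Φ(14/7.20 − 1.645) = 0.617.
- n = 20: SE = 6.64; Φ(14/6.64 − 1.645) = 0.678.

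| Evaluable per group | One-sided 5%, normal | One-sided 5%, t | One-sided 2.5%, normal | One-sided 2.5%, t |
|---|---|---|---|---|
| 17 (40 enrolled, 15% dropout) | 61.7% | 60.2% | 49.3% | 47.0% |
| 20 (40 enrolled, no dropout) | 67.8% | 66.5% | 55.9% | 53.8% |
| 27 (64 enrolled, 15% dropout) | 78.9% | 78.0% | 68.8% | 67.2% |

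The 2.5% columns apply if non-inferiority is judged from the 95% confidence interval that Statistical analyses says will be reported. With 17 per group, the half-width of that interval is about 1.96 × 7.20 = 14.1, slightly more than the margin. An observed difference of exactly zero would then not establish non-inferiority.

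**4. Risk of a missed conclusion.** At one-sided 5% and a true difference of zero, the risk rises from the planned 20% to about 32% with no dropout (100 − 67.8) and about 38% with 15% dropout (100 − 61.7).

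**The case against.** The strongest reply is that 40 may be an uncorrected leftover. If 64 are recruited, power is about 79%, essentially as planned, and the errors lie in the abstract and the eligibility section. That is possible, and it makes the power loss conditional on 40 being the true target. It does not remove the contradiction. It is also fair to say that the sample size section uses 80% as an input to a calculation yielding 32 per group and never claims 80% for 40 patients. The misleading impression arises when it is read with the enrolment figure and the Discussion.

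A second reply is that the planned ANCOVA will be more precise than the unadjusted calculation. The calculation takes no credit for this and gives no covariate correlation. To reach 80% at one-sided 5%, the residual SD would have to fall from 21 to about 17.8 with 20 per group, or 16.4 with 17. The adjustment factors named in the Discussion do not include baseline pain. Suppose baseline pain were adjusted for, with equal variances and a baseline-to-final correlation between 0.3 and 0.7 (an assumption, not in the document). The residual SD would be 21 × √((1 + r)/2), and power would be about 68% to 78% with 17 per group and 74% to 83% with 20. Adjustment could therefore narrow the gap, but it reaches 80% only in the most favourable part of that range.

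A third reply is that patients who discontinue are invited to the later assessments, so 15% dropout need not mean 15% missing data. This is true, and it is why the no-dropout figure is shown. Power is still only 68% with complete data on all 40.

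**Conclusion.** The concern holds. The document states two incompatible sample sizes, 64 and 40. Its own inputs support 64, and the power they imply is not reached at 40. For 40 enrolled, an unadjusted comparison with SD 21, margin 14, a true difference of zero and one-sided 5% alpha has about 62% power with 15% dropout and 68% with none. Judged from a two-sided 95% interval, the figures are about 49% and 56%. The Discussion's statement on adequate power is not true for the enrolment stated. Enrolment and power for the primary outcome are core design facts, so this must be corrected.

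**What to change.** Decide which number is the recruitment target and make every section agree.

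- **If the target is 64:** change 40 to 64 in the abstract and in Inclusion and exclusion criteria. If 40 is only a leftover, this is a text correction. If recruitment has actually been aimed at 40, moving to 64 means 24 more patients. Trial status says recruitment was under way at submission.
- **If the target is 40:** keep the calculation as the number that 80% power would have required, and say plainly that 40 will be enrolled and why. State the resulting power as about 62% (34 evaluable, SD 21, margin 14, one-sided 5%, true difference zero, unadjusted), with 68% if there are no losses. Delete the adequate-power statement from the Discussion. This needs no extra patients. The cost is a less favourable but accurate power statement.

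In either case, state the sidedness of the 5% alpha and the confidence interval from which non-inferiority will be judged, because the power depends on it. The registry record was not available for this review; its target should be checked against the figure chosen.

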### Statistical analyses

The data distributions of normality will be evaluated by the Kolmogorov–Smirnov test. In the case of normal distribution, an analysis of covariance (ANCOVA test) with Tukey’s post hoc will be used to test the differences between groups. The between-group mean difference, 95% confidence interval, and effect size (Cohen’s f) will be reported. The Kruskal–Wallis test will be used for non-normal data distribution, and the effect size will be calculated with Cohen’s r. All participants will be included in the analysis following an intention-to-treat approach.

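### The 32 per group reproduces only at an undeclared one-sided 5% level, while the only interval planned is a 95% CI; if that interval decides non-inferiority, power is about 69%, not 80%

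*Protocol article*

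**What the plan says.** Under Sample size estimates, the protocol article says that "a sample size of 32 patients per group would be necessary to test our research hypothesis on the primary outcome (knee pain"). The inputs are "an intergroup variability (σ) in the VAS gain of 21% for both groups", "a non-inferiority limit (d) of 14" per cent, "a type-I error of 5" per cent, and "a power of 80% (β=0.20) and a dropout rate of 15" per cent. It does not say whether the 5% is one-sided or two-sided.

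Under Statistical analyses, an ANCOVA is planned to test for differences between the groups. The reported results are to include the mean difference, its "95% confidence interval, and effect size". No 90% or one-sided interval is named, and no rule compares any interval with the 14% limit.

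The Abstract (Methods) and the Inclusion and exclusion criteria both set enrolment at 40 patients in total, not 64.

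**The concern.** A non-inferiority conclusion depends on whether one confidence bound clears the margin. A one-sided 5% test uses the bound of a 90% CI, and a 95% CI gives the stricter one-sided 2.5% test. Sample size and analysis should therefore use the same level. Here the calculation appears to use one level, and the only interval planned uses the other.

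Two things are at stake. The stated 80% power may not apply to the inference that readers will draw from the reported interval. And for a result near the limit, the 90% bound may clear 14 while the 95% bound does not, with no sentence in the article to say which of them settles the question.

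**Working it through.** **Inputs from Sample size estimates:** SD of VAS gain 21, limit 14, power 80%, dropout 15%, 32 per group. I read both percentages as points on the 0–100 VAS; only their ratio, 21/14 = 1.5, enters the formula.

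**Assumptions not stated in the document:** true difference 0, 1:1 allocation, unadjusted comparison, normal approximation.

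**Step 1. Reproduce the 32.** Evaluable patients per arm: n = 2(z₁₋α + z₁₋β)²(σ/d)².

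- One-sided 5%: 2(1.645 + 0.8416)²(1.5)² = 27.82, and 27.82 × 1.15 = 31.99. This is the stated 32.
- One-sided 2.5% (two-sided 5%): 2(1.960 + 0.8416)²(1.5)² = 35.32, so 36 evaluable. 36/0.85 = 42.4, so 43 enrolled; 36 × 1.15 = 41.4, so 42. Neither is 32.
- Two-sided equivalence (two one-sided tests at 5%): 2(1.645 + 1.2816)²(1.5)² = 38.5, so 39 evaluable before any dropout. Not 32.

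Of these standard variants, only one-sided 5% gives the stated figure.

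**Step 2. Power under each interval.** Power = Φ(d/(σ√(2/n)) − z₁₋α). For 32 enrolled with 15% loss, n = 32 × 0.85 = 27.2 and d/(σ√(2/n)) = 2.458.

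- 90% CI: Φ(2.458 − 1.645) = 79.2%
- 95% CI: Φ(2.458 − 1.960) = 69.1%

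| Evaluable per arm | How reached | One-sided 5% / 90% CI | One-sided 2.5% / 95% CI |
|---|---|---|---|
| 32 | 32 enrolled, no loss | 84.7% | 76.0% |
| 27.2 | 32 enrolled, 15% loss | 79.2% | 69.1% |
| 20 | 40 in total, no loss | 67.8% | 55.9% |
| 17 | 40 in total, 15% loss (20 × 0.85) | 61.7% | 49.3% |

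The noncentral t distribution gives slightly lower values: at 27.2 evaluable, 78.3% and 67.5%.

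**Step 3. Dropout (side note).** Multiplying by 1.15 does not exactly offset a 15% loss: 32 × 0.85 = 27.2, just under 27.8. Dividing gives 28/0.85 = 32.9, so 33. The difference is one enrolled patient per arm and about 1 point of power (79.2% against 80%).

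**The case against.** The strongest reply is that no figure is miscalculated. One-sided 5% is a natural level for a non-inferiority limit, and it gives 32. A 95% CI can be reported descriptively beside a one-sided 5% decision, and a condensed article may leave the decision rule to a fuller document. This stands in part. A reader might infer that the trial simply has 69% power instead of 80%, but the article never says that the 95% CI is compared with the limit, so the 69% holds only on that reading. What the reply leaves untouched is that the article itself gives an alpha without sidedness and an interval at a different level from the one behind its sample size.

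A second reply is that ANCOVA could recover power. If baseline VAS were a covariate and variances were equal at both times, the residual SD would be 21 × √((1 + r)/2), where r is the correlation between baseline and follow-up. At 27.2 evaluable per arm, power with the 95% CI would then be about 86% at r = 0.3, 81% at r = 0.5 and 76% at r = 0.7. So it cannot be said that 80% is out of reach under every analysis. But the article does not name baseline VAS as a covariate. The Discussion lists only sex, unilateral or bilateral disease, and medication use as adjustment factors, and the sample size section claims no gain from adjustment.

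Two other stronger readings also fail. A reader might call the dropout step a material error; Step 3 shows that it is not. A reader might infer that the authors mean to choose between a 90% and a 95% interval after seeing the data; the article names only the 95% interval and offers no such choice. The gap is that its role is not stated.

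Finally, the conflict between 64 patients required and 40 planned matters more for power than the choice of interval. That is true, but it does not settle this point: at 17 evaluable per arm the two intervals still differ by about 12 points of power.

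**Conclusion.** The point holds as a mismatch between the sample size calculation and the planned inference. The 32 per group rests on an undeclared one-sided 5% level, which corresponds to a 90% CI, and the only interval in the plan is a 95% CI.

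If the 95% CI decides non-inferiority, unadjusted power at 32 per group is about 69% with the protocol's own 15% loss and 76% with none, and 80% would need 43 enrolled per arm, 11 more than stated. If a one-sided 5% test decides, power is about 79%, close to the stated 80%.

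These figures rest on a true difference of 0, 1:1 allocation and no gain from covariate adjustment. They also assume that 32 per group are enrolled; at 40 in total with 15% loss they fall to about 49% and 62%.

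**What to change.** 1. In Sample size estimates, state whether the 5% is one-sided or two-sided.
2. In Statistical analyses, name the interval that is compared with the 14-point limit.
3. Restate power to match. With a one-sided 5% test and 90% CI, it is about 79% at 32 per group (33 per group restores 80%). With the 95% CI, it is about 69% at 32 per group, or 43 per group are needed for 80%.
4. Give the same figure for the stated enrolment of 40 (about 62% or 49% at 17 evaluable per arm), so that power is not quoted only for a 64-patient trial.
5. Say whether adjustment for baseline VAS is assumed. If it is, state the correlation used and recompute.

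The cost is a few sentences in two sections and a less favourable power statement. No extra patients are needed if power is restated; keeping 80% with the 95% CI and no adjustment would take 86 in total. The choice should be fixed before outcome data are seen by group.
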